**9.6 Criteria for Permanent Treatment Discontinuation for an Individual Participant**

The criteria for permanent treatment discontinuation of further study product/intervention(s) for an individual participant are:

- Treatment-related toxicity (see section 9), including pelvic inflammatory disease, deep epithelial disruption
- Requirement for prohibited concomitant medications such as oral antibiotics
- Pregnancy or breastfeeding
- Completion of treatment as defined in the protocol
- Request by participant to terminate treatment
- Clinical reasons believed life-threatening by the physician even if not addressed in the toxicity section of the protocol
- Unwillingness or inability to remain abstinent for the duration of the study.

The participant will continue to be followed with participant’s permission if study product/intervention (s) is discontinued.

**9.7 Criteria for Premature Study Discontinuation for an Individual Participant**

The criteria for premature discontinuation from the study for an individual participant are:

- Participant repeatedly non-compliant with study treatment as prescribed (missing more than three doses of study product throughout the 14 days of product use)
- Pregnancy or breastfeeding
- Request by participant to withdraw
- Request of the primary care provider if s/he thinks the study is no longer in the best interest of the participant
- Participant judged by the investigator to be at significant risk of failing to comply with the provisions of the protocol as to cause harm to self or seriously interfere with the validity of study results
- At the discretion of the IRB, Food and Drug Administration, NIH, investigator, or pharmaceutical supporter.

## 10.0 STATISTICAL CONSIDERATIONS

## 10.1 Overview and Statistical Designs Issues

## All subjects who receive treatment (1% tenofovir gel or matched placebo gel) will be included in all analyses. The primary objective of this study is to assess the mucosal response to repeated applications of 1% tenofovir gel or matched placebo gel by examining cervicovaginal secretions for cytokines chemokines, defensins, SLPI and lactoferrin as well as changes in the cell population in CVL pellets. A secondary objective is to assess whether the intrinsic antimicrobial (HSV, *E. coli* and *Staph aureus*) activity of CVL is altered following 14 days of daily intravaginal use of 1% tenofovir gel or matched placebo gel and correlate any observed changes in antimicrobial activity with changes in levels of mediators of mucosal immunity. An exploratory objective is to measure and compare the levels of tenofovir detected in serum and CVL.

The outcome is the level of individual proteins obtained after application of drug compared with placebo gel or total number of white blood cells and of specific cell types in CVL pellets. Differences between groups with respect to age and baseline amounts of mediators will be compared by *t* test. Differences between groups with respect to change in cytokines, chemokines, mediators of mucosal immunity, cell numbers, and antimicrobial activity will be compared by analysis of covariance and adjusted for baseline (after log transformation of data for cytokines, chemokines, and mucosal mediators). Differences between groups with respect to change in fold reduction in viral or bacterial infection after application of drug or placebo gel relative to titers in screening CVL samples will be determined by Wilcoxon nonparametric test (with exact p-values) on log transformed data. Calculations will be done using SAS software (version 9; SAS Institute).

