**3.2 Secondary Objectives**

A secondary objective is to determine whether the intrinsic antimicrobial activity of CVL to HSV, *E. coli* and *Staphylococcal aureus* is altered following 14 days of daily intravaginal application of 1% tenofovir or matched placebo gel compared to antimicrobial activity at baseline. If changes are observed, we will explore whether changes in the concentration of specific mediators correlate with the observed change in antimicrobial activity.

An exploratory objective is to measure the concentration of tenofovir in serum, CVL and cells following repeated daily intravaginal application of 1% tenofovir gel.

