At the screening visit, eligible volunteers will come to the General Clinical Research Center (GCRC) at the Montefiore Medical Center (MMC)/Albert Einstein College of Medicine (AECOM). After informed consent is obtained, a medical, gynecological, and sexual history will be obtained. Urine will be collected for microscopy, culture, and a pregnancy test. If the pregnancy test is negative, a pelvic examination will be performed including a speculum exam with visual inspection, pH measurement, wet prep, and collection of a baseline cervicovaginal lavage (CVL) sample. CVL is a wash of the cervicovaginal area using 10 ml of phosphate buffered saline (PBS). A 10 ml syringe filled with PBS is aimed directly at the cervical os and posterior vaginal wall. The pooled fluid is aspirated and the entire volume collected. A Pap smear will be obtained if documentation of a negative result within the last year is not available. A cervical swab (DNA probe) for *N. gonorrhoeae* and *C. trachomatis* will be done. A bimanual exam will be performed for adnexal masses or tenderness. If there is evidence of a clinically detectable genital abnormality (i.e., ulcer, lesion or positive wet mount) or urinary tract infection, appropriate treatment and follow-up will be provided and the volunteer will be ineligible to continue in the study at this time. If a lesion or ulcer is present at this or any visit, a herpes culture will also be sent. Blood will be collected for a pregnancy test, HIV EIA, RPR, HSV serologies (type common and type-specific; Focus Technologies, Herpes Select), hepatitis B surface antigen, hepatitis B core immunoglobulin M (IgM) and hepatitis B core immunoglobulin G (IgG) (See Appendix I). Blood will also be collected for progesterone and estradiol levels to determine the phase of menstrual cycle (proliferative phase defined by serum progesterone  3 ng/ml) and to assess kidney and liver function. Subjects with no contraindications to study participation will be presumed eligible for enrollment.

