On the day of Enrollment (Day 0) (2-6 days after the next menses, within 30 days of screening), participants will return to the GCRC. Test results from screening will be reviewed. Urine will be collected for a repeat pregnancy test. If the pregnancy test remains negative, a speculum exam will be performed and the vagina and cervix will be visually inspected. A pH sample from the vaginal wall and a gentle swab for wet prep will be obtained. If there is evidence of a clinically detectable genital abnormality (i.e., ulcer, lesion or positive wet mount) appropriate treatment and follow-up will be provided and the participant will be ineligible to participate further at this time. If there is evidence of recent intercourse (sperm visualized on wet mount slide or positive PSA-specific membrane test), the participant will be ineligible to continue in the study. If there is evidence of acute or chronic hepatitis B infection or liver or kidney abnormalities, the participant will be ineligible to continue in the study. If the patient is eligible, a baseline CVL will be collected. Participants will be randomized in a double blind manner to receive the 1% tenofovir gel or matched placebo gel. The participant will insert one dose of study gel intravaginally under the guidance of the study clinician. Provided that the first dose is well tolerated, subsequent applications will be inserted once daily (preferably at bedtime) by the participants (see Appendix III) for 13 consecutive days. Subjects will be instructed and frequently reminded to apply each daily dose at bedtime. Study gels will be provided in single-use tubes with separate vaginal applicators and the participant will be provided with a study diary to record usage, symptoms and reasons for non-adherence.

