## Clinical Procedures

- Obtain informed consent.
- Assign Participant ID.
- Collect demographic and locator information.
- Collect sexual history.
- Collect medical history and concomitant medication information.
- Provide HIV/STI pre-test counseling.
- Collect blood for pregnancy test, HIV EIA, RPR, herpes serology, hepatitis B surface Ag, hepatitis B core IgM and IgG.
- Collect blood for progesterone and estradiol, liver and kidney function.
- Collect urine for HCG pregnancy test; provide participant with result.
- Collect urine for microscopy and culture.
- Perform pelvic examination including:
- Speculum examination of vagina and cervix,
- Collection of pH sample from the vaginal wall
- Swab from anterior or lateral fornix for wet prep (two samples of discharge on slide for saline prep, potassium hydroxide prep and whiff test), and PSA-specific membrane test for semen (One-Step ABA card PSA, Abacus Diagnostics, West Hills, CA)
- Collection of baseline CVL,
- Pap smear (if documentation of a negative result within the past year is not available),
- Cervical swab (DNA probe) for *N. gonorrhoeae* and *C. trachomatis*,
- If ulcerative lesions are noted, collect swab for herpes simplex virus culture,
- Bimanual exam for adnexal masses or tenderness.
  - If participant determined to be ineligible, end visit and complete all required data collection forms. If participant remains presumptively eligible, schedule Enrollment Visit to occur 2-6 days following menses within 30 days after the Screening Visit.
- Instruct participant not to use vaginal products and to abstain from sexual intercourse for 48 hours prior to the Enrollment Visit.
- Complete all required data collection forms.

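### Antimicrobial activity has two unranked analyses, 'baseline' is undefined, and the ANCOVA's log transformation omits this endpoint and cell numbers

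*Protocol*

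**What the plan says.** **The two analyses.** Protocol Section 10.1 lists the variables whose between-group differences go to ANCOVA, and the list ends: "cell numbers, and antimicrobial activity will be compared by analysis of covariance and adjusted for baseline". A parenthesis limits the transformation: "after log transformation of data for cytokines, chemokines, and mucosal mediators". The next sentence takes the fold drop in viral or bacterial counts and says that its change "relative to titers in screening CVL samples will be determined by Wilcoxon nonparametric test (with exact p-values) on log transformed data". Section 4.1 describes one set of functional assays (HSV-2 plaques, *E. coli* and *S. aureus* colonies), so both sentences concern the same data.

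**The reference sample.** Section 3.2 states the secondary objective as activity after 14 days "compared to antimicrobial activity at baseline", with no visit named. Section 4.0 describes the screening visit as including "wet prep, and collection of a baseline cervicovaginal lavage (CVL) sample", and the screening list in Section 7.1 also calls that sample baseline. Section 4.0 then says of Day 0: "If the patient is eligible, a baseline CVL will be collected".

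**Control of the two samples.** Day 0 falls 2–6 days after menses and within 30 days of screening. At screening the woman is told to "abstain from sexual intercourse for 48 hours prior to the Enrollment Visit", so the restriction begins after the screening lavage has been taken. Section 5.2 excludes women who are menstruating at either visit and sets no other cycle window for screening.

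**The concern.** Two tests of one endpoint, with no order between them, can give two answers. Section 2.1 uses antimicrobial activity to judge whether mediator changes have functional significance, so which answer is reported affects how the whole study is read.

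The scale is a separate problem. The parametric test, which needs a log scale for skewed counts, is not given one for antimicrobial activity or cell numbers, while the rank test in the next sentence is. For cell numbers this reaches the primary objective, because Section 10.1 includes changes in the CVL cell population there.

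**Working it through.** **1. The plan's own figure.** Section 10.2 gives 12 per arm, SD about 0.5 log units, difference about 0.55, 80% power and two-sided 0.05, for immune mediators.
- n per arm = 2(1.960 + 0.842)² × 0.5² / 0.55² = 12.97, so 13 against the stated 12.
- Power at 12 per arm is 76.9% by the normal approximation and 73.1% by the t test. The difference detectable at 80% is 0.572 or 0.598.
- ANCOVA with a baseline correlation near 0.4 recovers the stated value: 0.598 × √(1 − 0.16) = 0.548.

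The stated figure is therefore about right for a log-scale, baseline-adjusted analysis. No such figure exists for antimicrobial activity or cell numbers.

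**2. Change score against ANCOVA.** With SD σ at both visits and correlation r, a change score has SD σ√(2(1 − r)), and ANCOVA has residual SD σ√(1 − r²). With σ = 0.5:

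| r | change score | ANCOVA |
|---|---|---|
| 0.2 | 0.632 | 0.490 |
| 0.5 | 0.500 | 0.433 |
| 0.7 | 0.387 | 0.357 |

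**3. Simulated power.** 20,000 trials per row, 12 per arm, log-normal data, SD 0.5 log10, true difference 0.55. Assumptions: the correlations shown between the post-dose value and each earlier sample, and a screening-to-Day 0 correlation of 0.8 times the larger of the two. The raw-scale ANCOVA is taken to use Day 0. 'Disagree' compares raw ANCOVA with Wilcoxon on change from screening.

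| r Day 0 | r screening | log ANCOVA, Day 0 | log ANCOVA, screening | raw ANCOVA, Day 0 | Wilcoxon, change from screening | Wilcoxon, change from Day 0 | disagree |
|---|---|---|---|---|---|---|---|
| 0.3 | 0.3 | 75.3% | 75.2% | 46.4% | 54.7% | 54.6% | 38.4% |
| 0.5 | 0.3 | 82.4% | 74.8% | 51.2% | 54.5% | 69.4% | 37.7% |
| 0.5 | 0.5 | 82.7% | 82.6% | 50.8% | 68.9% | 68.6% | 40.4% |
| 0.7 | 0.3 | 93.7% | 74.5% | 63.6% | 54.6% | 88.8% | 37.0% |
| 0.7 | 0.5 | 93.8% | 82.2% | 63.0% | 68.9% | 88.7% | 36.9% |

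With the screening correlation lowered to 0.2, Wilcoxon on change from screening falls to 48–49%, while log ANCOVA on that same sample still has 73%.

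**4. Where the Wilcoxon shortfall comes from.** Take log ANCOVA on Day 0 minus Wilcoxon on change from screening. Then ask how much is recovered by moving to ANCOVA on the same screening sample:
- 0.3/0.3: 20.5 of 20.6 points
- 0.5/0.3: 20.3 of 27.9
- 0.5/0.5: 13.7 of 13.8
- 0.7/0.3: 19.9 of 39.1
- 0.7/0.5: 13.3 of 24.9

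Counted this way, the unadjusted change score explains most of the loss in every row. The split depends on the order of the steps. At 0.7/0.3, moving Wilcoxon to Day 0 first recovers 88.8 − 54.6 = 34.2 points. The sample therefore matters a great deal only if Day 0 is much better correlated, and the documents do not say whether it is.

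**5. No true effect.** At least one of the two tests is significant in 7.2–7.5% of trials per assay.

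**The case against.** **Two different baselines.** A reader might infer that the two sentences use different samples. The documents do not say so. The ANCOVA visit is unnamed and the screening lavage is itself called baseline, so both sentences could mean one sample. What stands is that the term is undefined.

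**An uncontrolled or biased reference.** This is also tempting and also too strong. At screening, menstruating women and those with an abnormal wet mount are excluded, a PSA test is run, and progesterone and estradiol are measured. What screening lacks is a cycle window and an abstinence requirement. Both arms share that reference under randomization, so the cost is precision.

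**Loss caused by cycle-phase or semen noise.** The documents give no correlation for either sample, and step 4 shows that the change score alone can produce most of the gap.

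**Other defences.**
- The log parenthesis names what is logged and does not order a raw analysis of the rest. Section 4.1 also speaks of relative colony numbers, so the ANCOVA variable may already be a ratio to control. This softens the raw-scale reading for antimicrobial activity, but it gives no log scale and does nothing for cell numbers.
- An exact rank test is defensible at 12 per arm, especially as Section 4.1 foresees too few cells in some samples. That supports keeping it as a sensitivity analysis.
- A SAP often settles such details. Here, however, the protocol itself fixes two competing analyses, and a SAP would have to override or demote one.
- Antimicrobial activity is secondary in a 24-woman Phase I study, and the error inflation in step 5 is small. This argues against a higher rating.

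**Conclusion.** The point holds in this form. Section 10.1 prescribes two between-group analyses of the same assays without ranking them, leaves baseline undefined, and names a log transformation that omits antimicrobial activity and cell numbers. In every scenario tried, both analyses as written had less power than log-scale ANCOVA on Day 0: about 46–64% and 48–69%, against 75–94%. They disagreed on significance in about 37–40% of trials.

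These sizes rest on assumed log-normality, an SD of 0.5 log10 borrowed from the mediators, an effect of 0.55 and assumed correlations of 0.2 to 0.7. They show direction and rough scale and are not the trial's actual power. The overlap and the omission are plain in the text; the amount of power lost is not known. Should-fix.

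**What to change.** Replace the two sentences in Section 10.1 with one rule:
- Define baseline as the pre-dose Day 0 lavage throughout, and call the earlier sample the screening CVL in Sections 4.0 and 7.1.
- Name ANCOVA on the log10 value, adjusted for the Day 0 log10 value, as the main analysis of antimicrobial activity (relative to control) and of cell numbers, at the post-dose visits already assayed.
- State in advance how zero or sparse counts are handled.
- Keep the exact Wilcoxon test as a sensitivity analysis on change from Day 0, which also covers sparse counts.

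The cost is wording only: Section 7.1 already has these assays run on the Day 0 lavage, so no sample or visit is added. The downside is that cell-count results with many zeros may depend somewhat on the zero rule, which is why the rank test should stay alongside.

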**10.2 Sample Size Considerations**

There are limited published data regarding intra- and inter-subject variability with respect to soluble mediators detectable in CVL. We recently completed a study (NIH Protocol MSPRO 020 Effect of Repeated Application of PRO 2000 Gel on Inflammatory Mediators in Cervicovaginal Secretions) [24] that involves 24 low risk HIV-negative women and includes repeated measures of each of the cytokines, chemokines, SLPI and defensins using the identical assays proposed in this study. Based on the standard deviations obtained for most immune mediators in that study (~ 0.5 log units), the proposed sample size of 12 in the tenofovir group and 12 in the placebo group will allow us to detect with 80% power (based on a two-sided test with a type I error of .05), a difference of ~ 0.55 log units for each of these measures between groups.

**10.3 Enrollment/Randomization/Blinding Procedures**

The randomization will be 1:1 (i.e., 12 in each treatment arm). The MMC/AECOM Research Pharmacy will provide the randomization procedure. Throughout the period of study implementation and data analysis, neither study staff nor participants will be informed of the participants’ random assignments.

Both study gels will be supplied in identical, single-use tubes, and single-use applicators packaged in individual wrappers. Study staff and participants will be unblinded after all study visits and data analyses are completed. Individual exceptions may be considered by the PI and NIH Medical Officer in situations where product information may be needed to protect the safety of the participant.

**10.4 Participation Enrollment and Follow-Up**

Twenty-four healthy women will be enrolled in this study. Participant accrual will last approximately one year in this single-site study and each subject’s participation in this study will last approximately two months. Once a participant has enrolled in the study, the study site will make every reasonable effort to retain her for the complete study period. Given the relatively small study sample size, and the importance of ascertaining all outcomes among study participants, 100 percent retention of enrolled participants is targeted.

## 10.5 Data and Safety Monitoring

Close collaboration among protocol team members will be necessary to evaluate study progress and respond to occurrences of toxicity in a timely manner. Rates of accrual, adherence, follow-up, and AE incidence will be monitored closely by the protocol team on a regular basis. The team will meet weekly during the period of study implementation.

A Safety Committee composed of individuals unaffiliated with the study has been formed. The committee was carefully selected based on scientific and clinical backgrounds and has expertise in virology and clinical trials. Three physicians have been identified who will serve in this function well. [name]. is the Principal Investigator (PI) of the multi-center Women’s Interagency HIV Study (WIHS). [name]. has several years experience conducting clinical trials. [name]. is the Director of Clinical Research in the Department of Obstetrics & Gynecology and Women’s Health and has extensive gynecologic experience. The Committee will review safety and trial progress and provide advice with respect to study continuation, modification and/or termination. In order to achieve a timely evaluation of patient safety, the PI will submit a brief case report form, filled out at each visit, to the Safety Committee every 3 months during the study. All serious adverse events will be reported to the Committee, the MMC/AECOM IRB, Gilead Sciences, Inc. and the NIH NIAID/DAIDS Medical Officer within 24 hours of diagnosis.  The Safety Committee will review these data for safety parameters at least every 3 months or more often as necessary (for instance if any serious adverse event occurs).  The Committee will organize a meeting if toxicity becomes an issue in between scheduled semi-annual meetings.  The Committee will report any safety concerns to the PI, MMC/AECOM IRB and the NIH NIAID/DAIDS Medical Officer.

**10.6 Safety Review**

The PI is responsible for continuous close monitoring of all AEs that occur among study participants. For this study, accrual will be suspended if two or more study participants experience similar grade 3 or higher AEs (as defined by the DAIDS Table for Grading Severity of Adverse Experiences) judged possibly, probably, or definitely related to product use. The protocol team, in collaboration with the Safety Committee and NIH NIAID/DAIDS Medical Officer, will review all pertinent data and determine whether to continue accrual and product use. A decision to stop the study may be made by the team at this time, or at any such time that the team agrees that an unacceptable type and/or frequency of AEs has been observed.

## 11.0 DATA HANDLING AND RECORDKEEPING

**11.1 Data Management Responsibilities**

The study will be conducted in full compliance with the protocol. The protocol team will develop study case report forms. Data management will be performed at AECOM. Close collaboration among protocol team members will be necessary to evaluate study progress and respond to occurrences of toxicity in a timely manner. Rates of accrual, adherence, follow-up, and AE incidence will be monitored closely by the protocol team on a regular basis. The team will meet weekly during the period of study implementation. In addition, close cooperation between the protocol team members, personnel from NIH and pharmaceutical supporters will be necessary in order to track study progress, respond to queries about proper study implementation, and address other issues in a timely manner.The Division of AIDS at NIAID will hold the Investigational New Drug (IND) applications for this study under IND #55,690. Assignment of all sponsor responsibilities for this study will be specified in a Clinical Trials Agreement executed between Gilead Sciences, Inc. and the Division of AIDS, NIAID.

